**Figure 3: Study Protocol Flow**

## 4.2 Scientific Rationale for Study Design

In 2018, a case report documented that a single dose of nebulized tranexamic acid (TXA) prevented operative management in a three-year-old with PTH^10^. A subsequent randomized controlled trial in adults documented a decrease in blood loss and secondary hemorrhage using nebulized TXA for hemoptysis^20^. The current use of antifibrinolytics (e.g., TXA or e-aminocaproic acid) is rarely used to treat PTH. Therefore, there is an essential need to test the efficacy of nebulized TXA to decrease the severity of PTH. Our retrospective cohort study documented that nebulized TXA may be effective in decreasing the need for operative intervention^13^. However, retrospective studies have significant bias indicating the need for a multi-center, randomized, double-blinded, controlled clinical trial. As we do not have an established alternative drug the standard is to test the drug vs. a placebo such as nebulized normal saline. The power analysis and 1:1 study design reduces bias and confounders for the evaluation of study outcomes. Even if the patient presents without active bleeding, it is possible that nebulized TXA has the potential to stabilize the clot to prevent future bleeding.

A verified pulmonary PBPK model can set the dose of the phase 3 trial. A pulmonary PBPK model incorporates all known intravenous, oral, or local TXA administration PK and pulmonary physiology data. This model only needs verification by small number of systematic samples, compared to traditional pharmacokinetic studies that require multiple samples using different doses and ages of patient. A verified model can then be use predict the drug for the phase 3 trial with the lowest systematic absorption, which will minimize side effects.

## 4.3 Justification for Dose

We conducted a study evaluating nebulized TXA in 58 children with PTH^13^. Three consecutive doses of nebulized TXA were given to each child, 500 mg per dose for children >25 kg and 250 mg per dose for children <25 kg. These doses were picked from the earlier literature ^9,21^ that documented success in reducing hemoptysis. Our single-arm study demonstrated that nebulized TXA significantly decreased the need for surgical management of PTH by 44% compared to historical controls. There was no associated increase in adverse events or delays in care to patients who required a surgical intervention. This study found that some children responded after one dose, but most children responded after two doses. For the pilot trial, we propose to administer three doses of 500 mg (total 1500 mg) of nebulized TXA to each child enrolled regardless of their weight. This was further confirmed by a retrospective study that delivered 500 mg/dL to several children less than 7 years of age(3). We considered dose choice based on the need to balance the amount of TXA with a goal to decrease the severity of PTH. Using TXA improves our safety because it is an approved medication that has a minimal and known side effect profile.

We chose a total dose of 1500 mg because it does not exceed the maximum intravenous dose approved for the average weight of a four-year-old. Neurological and cardiac surgical procedures have used over 100 mg/kg intravenous loading dose of TXA and then 10 mg/kg/hour drip with minimal side effect^22,23^. We hope that nebulization to deliver TXA will result in a lower systematic peak of TXA and yet because it is focused on the source of the bleed it remains effective. Several studies have documented that peak TXA concentration is much reduced with topical versus intravenous administration^2425^. Lastly, the potential benefits of a higher dose of TXA is significantly less risk than risk of neurocognitive injuries documented by repeat exposures to anesthesia and surgery. In summary, the investigators chose a fixed dose based on the two points: 1) Nebulized TXA is expected to have very little systemic uptake, and we wish to maximize safe effect, and 2) Prior surgical studies have not shown an increased risk of AEs with intravenous TXA compared to placebo.

## 4.4 End of Study Definition

Study drug or placebo will also be discontinued if a severe anaphylactic reaction during or after administration.   All participants will be followed adverse events, need for surgical control of PTH, and patient-related outcomes for up 7-30 days from receipt of study drug.

# 5 Study Population

## 5.1 Inclusion Criteria

1. Received a tonsillectomy

2. Presents to the ED with secondary* post-tonsillectomy hemorrhage

3. Children between age of 2 to 17 years of age (i.e., before their 18^th^ birthday)

*Secondary post-tonsillectomy hemorrhage is defined as greater than 24 hours from their primary tonsillectomy operation (arrival in recovery/PACU).

## 5.2 Exclusion Criteria

1. Known and documented bleeding or clotting disorder

2. Known pregnancy

3. The patient is a ward of the state

4. Patients with known hypersensitivity or allergic response to tranexamic acid

5. Parents or guardians that cannot communicate in English or Spanish.

6. Intubation prior to enrollment

7. Previously enrolled patients

## 5.3 Lifestyle Considerations

Prior to performing a tonsillectomy, otolaryngologists will routinely screen all females who are at childbearing age for pregnancy. Thus, significantly decreasing the risk of enrolling an unsuspecting female who is pregnant. Furthermore, the risk of tranexamic use in pregnant females is minimal and unlikely because the use of oral tranexamic acid for the long-term prophylaxis of bleeding in pregnant females is well documented to be safe and effective^21^. There is no evidence from animal studies that tranexamic acid has any teratogenic effect or risk to the fetus (Category B). Reproductive studies have been performed in mice, rats, and rabbits and have no evidence of impaired fertility or risk to the fetus. Lastly, the investigators are concerned that imposing this exclusion criterion will reduce enrollment.

It is also possible that non-steroid anti-inflammatory drugs would influence the bleeding outcomes of the study participants. However, a 2013 updated systematic review and meta-analysis of 36 randomized controlled trials documented no significant differences in rates of bleeding or reoperation in patients receiving NSAIDS post-tonsillectomy^2^.

## 5.4 Screen Failures

**Missed eligible** patients are those who meet inclusion and exclusion criteria but are not enrolled. We will ask for a waiver of consent to review and collect emergency department records at each site (up to 100 patient's) during the study period to determine if patients met eligibility criteria but were not enrolled into the study. This can be due to misunderstanding, misapplying, not meeting the exclusion criteria or other factors.

**Screen failures** are defined as participants that consent to take part in the clinical trial but are later found to be ineligible.  A minimal set of screen failure information must ensure transparent reporting of screen failure participants to meet the Consolidated Standards of Reporting Trials (CONSORT) publishing requirements and to respond to queries from regulatory authorities. Minimal information includes demography, screen failure details, eligibility criteria, and any serious adverse event (SAE). Individuals who do not meet the criteria for participation in this trial (screen failure) may be re-screened. Rescreened participants will be assigned a new ID number as it is a new encounter.

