# 4 Study Design

## 4.1 Overall Design

Our overall hypothesis for the phase 3 trial is that nebulized TXA will decrease the severity of bleeding and the need for repeat surgical intervention for PTH. To test this hypothesis, we first propose to conduct a multi-center, randomized controlled, blinded pilot trial (phase 2) to assess the feasibility, safety, and the local and systematic absorption of nebulized TXA in children with PTH. Safety and pharmacokinetic data are well known for topical and intravenous administration of TXA but there is limited data on nebulized delivery of TXA. Participants will be randomized at the time of the consent in the emergency department. Earlier PECARN studies experience suggest that pre-consenting patients in surgical clinic will not improve participant enrollment or completion. Children 2 to 17 years old presenting to the ED with PTH will be randomized in a 1:1 ratio to three doses TXA or placebo (saline).  All interventions will be blinded by the investigator, treating clinical care team, and research staff. Only the pharmacist and biostatistician will know the randomization schedule. We will not unblind patients as there is no reversal agent. Clinical teams will be asked to assume the patient received TXA. Patients will be followed during their hospital course and outcomes will be evaluated at seven +/- 1 days after randomization. As this is a pilot study, no stratification or interim analysis will be performed.

[figure not shown]

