# 6 Study Intervention

## 6.1 Study Intervention(s) Administration

### 6.1.1 Study Intervention Description

The intervention will not interfere with or supersede standard ED care for post-tonsillectomy hemorrhage. After determination of eligibility and obtaining informed consent, patients will be randomized to receive nebulized TXA or saline. The only change to ED PTH management is the addition of nebulized study drug. This randomized pilot trial will thus evaluate the feasibility to enroll patients into a trial that will determine the efficacy of nebulized TXA (investigational drug) compared to nebulized normal saline (placebo) to prevent repeat surgical intervention.

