## 7.2 Participant Discontinuation/Withdrawal from the Study

Participants are free to withdraw from participation in the study at any time upon request. A site investigator may discontinue or withdraw a participant from the study for the following reasons:

1. If any clinical adverse event (AE), laboratory abnormality, or other medical condition or situation occurs such that continued participation in the study would not be in the best interest of the participant.
2. Emergent intubation for respiratory failure.
3. If the participant meets an exclusion criterion (either newly developed or not previously recognized) that precludes further study participation.

The reason for participant discontinuation or withdrawal from the study will be recorded on the Adverse Event Case Report Form. Subjects who sign the informed consent form and are randomized but do not receive the study intervention may be replaced.  Subjects who sign the informed consent form, are randomized, and receive the study intervention, and later withdraw or are discontinued from the study, will no longer have data collected, but existing data collected prior to withdrawal will still be used. Subjects may be replaced as necessary depending about withdrawal.

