### 8.3.5 Adverse Event Reporting

Assuring patient safety is an essential component of this protocol. Each participating site investigator will have primary responsibility for the safety of the individual patients under his or her care. All adverse events occurring after study randomization for 30 days (+/- 5 days) will be recorded and entered the electronic data entry system into UTHSCSA REDCap for single site study and to the REDCap Database provided by the DCC for the multisite study. In accordance with local IRB requirements, the site investigator may be required to report such events to the IRB in addition to notifying the DCC.

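### With randomization at consent, the section 5.4 screen-failure definition falls mainly on children already randomized, and their data and enrolment status conflict with sections 7.2, 8.3.5 and exclusion 7

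*Protocol*

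**What the plan says.** Section 5.4 of the protocol describes screen failures as "defined as participants that consent to take part in the clinical trial but are later found to be ineligible". It does not say that the finding must come before randomization. The minimum record for such a child is demography, the reason for failure, the eligibility criteria and any SAE. Re-screening is permitted: "Rescreened participants will be assigned a new ID number as it is a new encounter".

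The order of events is given elsewhere. Section 6.1.1: "After determination of eligibility and obtaining informed consent, patients will be randomized to receive nebulized TXA or saline". Section 10.1.1.2 likewise has the guardian approached once the child is known to be eligible. Section 4.1: "Participants will be randomized at the time of the consent in the emergency department". Under section 6.3 the treatment is pre-assigned in a box, so that randomization does not hold up treatment.

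Three other rules reach the same child:

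- Section 7.2, item 3, lets the site investigator withdraw a participant: "If the participant meets an exclusion criterion (either newly developed or not previously recognized) that precludes further study participation". For a dosed child who is withdrawn, data to that date are used and nothing more is collected.
- Section 8.3.5: "All adverse events occurring after study randomization for 30 days (+/- 5 days) will be recorded".
- Exclusion 7 in section 5.2: "Previously enrolled patients".

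**The concern.** In most trials a screen failure is a person who consents, goes through a screening period and is never randomized. This trial has no screening period after consent. A definition that starts at consent and has no end point therefore describes, for the most part, children who already have an assignment and may have been nebulized.

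That leaves one child under several incompatible rules. The site has to decide whether the child is a screen failure or a withdrawal, whether non-serious adverse events, PK samples and the day-7 and day-30 contacts are still collected, and whether a later bleed belongs to the first enrolment or to a new ID. The choice is made after randomization, with knowledge of what happened to the child. What is at stake is the denominator of the feasibility endpoints, and safety, PK and day-7 data that cannot be recovered if they are not collected at the time.

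**Working it through.** **1. What can fall between consent and randomization.** Sections 6.1.1 and 10.1.1.2 place the eligibility check before consent, and section 4.1 places randomization at consent. Only the short gap between signature and opening the box remains. A finding of ineligibility after consent will therefore mainly concern a randomized child. Whether that child has been dosed depends on timing that the protocol does not give.

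**2. The rules side by side, for a randomized and dosed child later found ineligible.**

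| Question | Section 5.4 | Elsewhere |
| --- | --- | --- |
| Status | Screen failure | 7.2 item 3: possible withdrawal |
| Data before the finding | Only a reduced record is required | 7.2: existing data are used; 9.3: groups are formed by treatment received |
| Adverse events afterwards | SAEs required | 8.3.5: all events to 30 days; 7.2: no collection after withdrawal |
| Return to the ED | May be re-screened under a new ID | Exclusion 7: not eligible if enrolled before |

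The entries in the third row cannot all be followed. The fourth can be followed only if a screen failure does not count as enrolled, which the protocol does not say.

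**3. Effect on the enrolment criterion.** The plan's own figure (section 9.2) is 0.6 × 3 sites × 12 months = 21.6, rounded up to 22, which reproduces. Site-months: 3 × 12 = 36. (Section 9.1 gives 18 months for the multi-site study; I use the 12 months from which the 22 is derived.)

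- All 22 counted: 22/36 = 0.611 per site per month, above 0.6.
- One child left out: 21/36 = 0.583, below 0.6.
- Single-site study: 12/12 = 1.00 and 11/12 = 0.917, both above 0.6. The target of 12 would be missed, but not the rate.

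**4. Share of the data.** One child is 1/22 = 4.5% of the multi-site study or 1/12 = 8.3% of the single-site study. With 1:1 allocation this is 1/11 = 9.1% or 1/6 = 16.7% of one arm.

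**5. Effect on the delivery criterion (more than 90% with at least two doses).** If the reclassified child had fewer than two doses:

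- Multi-site: 19/22 = 86.4% (fails) becomes 19/21 = 90.5% (passes).
- Single-site: 10/12 = 83.3% (fails) becomes 10/11 = 90.9% (passes).

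These are borderline cases, chosen to show that the classification alone can decide the result.

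**6. How likely is a case?** The protocol gives no rate. With an assumed probability p per child, the chance of at least one case is 1 − (1 − p)^N:

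| Assumed p | N = 12 | N = 22 |
| --- | --- | --- |
| 2% | 21.5% | 35.9% |
| 5% | 46.0% | 67.6% |
| 10% | 71.8% | 90.2% |

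**The case against.** The best defence is that section 5.4 is a reporting rule, written for CONSORT and for regulators, and not an analysis rule. Its data list is a floor, so a site can meet it and still record every adverse event under 8.3.5. Section 9.3 groups children by treatment received, and 7.2 keeps the existing data of dosed children. Exclusion 7 already stops a second enrolment. Because eligibility is checked first, late findings should be rare, and some will come before the box is opened. How ineligible randomized children are analysed is normally left to the SAP.

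Much of this stands, and it rules out three stronger readings that a reader might infer:

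- *That section 5.4 removes these children from the analysis.* It does not say so, and 7.2 and 9.3 point the other way for children who were dosed.
- *That only their SAEs are kept.* The list also covers demography, failure details and eligibility criteria, and it is a minimum.
- *That the heaviest bleeders would be lost preferentially, lowering the rate of return to the OR.* Exclusion 1 covers only a bleeding or clotting disorder known and documented at entry, so one first found in the work-up does not make the child ineligible under section 5.2. The broader wording of 7.2 item 3 leaves a route open, but it is discretionary and keeps existing data. The pilot's outcomes are also descriptive (9.4.1), and return to the OR is not powered.

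What the defence does not meet is the conflict over status, ID and continued data collection. These are conduct rules that belong in the protocol, and an SAP cannot restore day-7, PK or adverse event data that were not collected. Exclusion 7 settles the re-screening question only if the protocol says that a randomized screen failure counts as enrolled.

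**Conclusion.** The point holds as a contradiction in the stated rules, not as a demonstrated bias. Section 5.4 lacks a before-randomization limit. In this design it therefore mainly describes randomized children, whose place in the enrolment count, delivery proportion, adverse event, PK and day-7 data is not consistently defined. Follow-up data can be lost by either route: the reduced record of 5.4, or the end of collection under 7.2.

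The size depends on an event whose frequency the protocol does not give. With no such child the effect is zero. With one, 4.5% of 22 or 8.3% of 12 children are affected. If that child is not counted, a multi-site study that just reaches its target moves from 0.611 to 0.583 per site per month and crosses the 0.6 go/no-go threshold. This assumes exactly 22 randomized over 36 site-months, and a team that reads screen failure as not enrolled. The protocol neither requires nor prevents that reading.

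**What to change.** In section 5.4, limit the term screen failure, and the permission to re-screen, to children who consent but are never randomized. That brings the section into line with exclusion 7.

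Add that a randomized child later found ineligible is recorded as an eligibility deviation, keeps the original ID and assigned arm, counts toward enrolment, and stays in adverse event, PK and 7- and 30-day data collection unless consent is withdrawn. Reword section 7.2, item 3, so that ineligibility recognized late does not by itself end data collection. This concerns data only; whether study drug continues in such a child is a clinical decision outside this point.

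The cost is a few sentences in an amendment. The chart review and follow-up contacts are already scheduled for every participant. The downside is that a few children who deviate from the criteria remain in the data; they can be left out in a sensitivity listing.

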## 5.5 Strategies for Recruitment and Retention

The pilot study aims to test the feasibility of enrolling 0.6 patients per site per month. The specific goal for this pilot trial is to enroll 12 patients (6 treatment groups & 6 control group) at the University of Texas Health Science Center (UTHSCSA)/University Hospital in San Antonio, TX. The participants will be children who present to the emergency department (ED) with secondary posttonsillectomy hemorrhage (PTH) occurring 24 hours or more after their tonsillectomy. PTH patients will be screened and approached in the ED. Participants will be followed as outpatients for one week post-randomization. Due to the short follow-up period, we do not expect a significant loss of participants. However, text, phone, and e-mail information will be obtained from each participant to give the study team multiple options for gathering data on secondary and tertiary objectives. In this pilot analysis, we will offer participants an incentive to complete all study procedures. We will also closely monitor study completion to determine if participant incentives are necessary for the main trial. This pilot study will help assess the feasibility of enrollment rates and the effectiveness of follow up methods, which will inform the design and implementation of the larger main trial.

The investigators will enroll at the University of Texas Health Science Center (UTHSCSA)/University Hospital in San Antonio, TX for the single site and the multi-site study, the University of California at Davis Medical Center in Davis, CA, and Hasbro Children’s Hospital in Providence, RI. Each of the ENT and ED colleagues at each site have provided the incidence of PTH, percentage that return to the OR, and the monthly ED visit rate. Previous studies document that PTH primarily presents at night, therefore we arrange for 24/7 coverage at each site.

| **Site** | **Annual PTH Incidence** | **Going to OR** | **Monthly ED Visits** |
| --- | --- | --- | --- |
| San Antonio, TX | 5.4% | 73% | 1.60 |
| Davis, CA | 3.2% | 70% | 0.63 |
| Providence, RI | 2.8% | 63% | 2.80 |

5.6 COSTS

The patient or their health insurance provider will bear the responsibility for the expenses associated with treatments and procedures that would be administered regardless of the patient's participation in this study, such as subsequent surgeries and hospital admissions. Please note that certain costs may not be covered by insurance providers (e.g., approved drugs used off-label). If the patient's insurance does not cover these treatments or procedures, the patient will be accountable for the associated expenses.

"The sponsor will supply the study drug/device at no cost to patients throughout the duration of this study.

5.7. COMPENSATION

Payment method: participants will receive compensation via an hsc debit card.

Compensation details:

- Visit 1: day 0-1
  - Type: one-time
  - Activity: initial visit
  - Amount: $50 (usd)
- Visit 2: day 7
  - Type: one-time
  - Activity: second follow-up visit
  - Amount: $25 (usd)
- Visit 3: day 30
  - Type: one-time
  - Activity: final visit
  - Amount: $25 (usd)

Timing: compensation will be provided immediately upon completion of each visit.

Minimizing coercion: the compensation structure has been carefully designed to avoid coercion or undue influence. The amounts offered are reasonable and commensurate with the time and effort required for each visit, ensuring that participants are not unduly influenced to participate.

Pediatric participants: compensation will be provided to the parent or legal guardian of the minor participant.

Prorated compensation: if a participant withdraws from the study before completion or if there are multiple research activities, compensation will be prorated accordingly based on the completed activities.

Reimbursement: participants may be eligible for reimbursement of travel expenses such as hotel accommodation or mileage. Reimbursement will be provided upon submission of receipts, and the reimbursement process will be explained during the informed consent process.

Escort reimbursement: there may be reimbursement available for escorts who accompany participants to study visits. Details regarding escort reimbursement will be provided upon request and will be subject to the study's reimbursement policy.

